**Aim 2c: To investigate whether presence of increased baseline and follow-up levels of p16^INK4a^ in women with normal colposcopy or CIN1 is associated with increased risk of detecting CIN2/3 during one-year follow-up.** HIV-infected women enrolled in care at the FACES clinics in western Kenya who have had baseline p16^INK4a^ measurement, with normal colposcopy or CIN1 will be followed-up after one-year for repeat testing for p16^INK4a^, HR-HPV and colposcopy to compare rate of CIN2/3 between the two groups.

Hypothesis 2: The ROC curves for the biochemical assay for p16^INK4a^ will define a cut-off level for a positive result that will provide a sensitivity and specificity for CIN2/3 greater than those for HR-HPV testing in this population.

Hypothesis 2c: The risk of detecting CIN2/3 at one-year in women with normal colposcopy or CIN1 is increased in women with increased levels of p16^INK4a^ in cervical specimens at baseline and/or follow-up compared to women with normal or undetectable levels of p16^INK4a^.

**Aim 3: To measure and compare the quantity of HIV-1 RNA in the cervicovaginal secretions of women with cervical dysplasia to those with normal cervical exams.** We will measure and compare the presence and levels of cervicovaginal HIV-1 in women with biopsy-confirmed high-grade cervical dysplasia to those of women with no evidence of cervical disease. Cervical dysplasia will be defined as cervical intraepithelial neoplasia 2 or 3, or CIN2/3.

**Aim 3a: To determine the amount and duration of increased HIV-1 RNA shedding in the genital tract following cervical biopsy for suspected dysplasia.** We will measure the presence and levels of cervicovaginal HIV-1 in women prior to undergoing cervical biopsy and compare values to specimens taken on days 0, 2 and 7 following biopsy.

Hypothesis 3: Women with biopsy-confirmed CIN2/3 have higher odds of detectable genital HIV-1 viral load. Women undergoing biopsy will have an increase in genital HIV-1 RNA shedding that will return to baseline within 7 days post-procedure.

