**Aim 4: To measure and compare the amount of HIV-1 RNA found in the cervicovaginal secretions in women before and after undergoing treatment for CIN2/3 with LEEP.**  Collection of specimens for detection and quantification of cervicovaginal HIV-1 viral load will be done immediately prior to the LEEP, and on post-procedure weeks 1, 2, 4, 6, 10 and 14 to determine the level and duration of increased genital shedding associated with the procedure.

Hypothesis 4: There will be a significant increase in HIV-1 genital shedding post-treatment which will return to baseline before 14 weeks post-treatment.

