**Specific Aim 4:** Sample size calculations for Aim 4 focus on estimation of the mean change in viral load between baseline and one week of follow-up. A sample size of 30 will provide sufficient power to address hypotheses of interest, and will also allow investigation of factors related to observed changes in viral load. We assume a standard deviation of 1.7 log copies for both the baseline and follow-up measure, that the correlation between the baseline and follow-up measure will be 0.7, and that change will be evaluated using a t-test for paired measurements. This calculation is based on variability estimates from Coombs et al., who examined genital tract shedding in 55 women using Sno-Strips, cytobrush and cervicovaginal lavage measures. They found Sno-Stripscalc to be the least variable measure, with a within-individual standard deviation of 0.55 log copies of viral RNA and a between-individual standard deviation of 1.66 log copies. Although preliminary data are not available to inform more detailed calculations, we anticipate similar levels of power to address hypotheses concerning post-treatment changes. With these assumptions, ***30* participants** should provide at least 80% power to detect within-individual changes (measured as the difference between pre and post-treatment levels) as small as 1 log as significant at the 5% level. Power to detect change as small as 1.5 logs will exceed 95%. These results indicate that we have sufficient power to detect clinically important changes, and will also be able to investigate patterns of change over the entire course of follow-up.

Study Design

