**Specific Aims 2c:** To compare the rate of detecting CIN2/3 at one-year follow-up between women with normal or increased levels of p16^INK4a^ at baseline, we will use the Pearson’s chi-square test to investigate any significant differences in the proportions. Based on our sample size calculations, we aim to have 80 percent power with a two-sided alpha of 0.05. To compare the rates of developing CIN2/3 at one-year follow-up between women with persistently elevated p16^INK4a^ compared to those with only one elevated measurement, we will also use the Pearson’s chi-square test to look for statistically significant differences in proportions of CIN2/3 in the two groups.

**Specific Aim 3:** To compare the presence and magnitude of HIV-1 genital shedding between women with and without cervical dysplasia we will compute the odds ratio of HIV-1 detection in genital secretions with 95% confidence intervals. Multivariate analyses will be performed using logistic regression to control for demographic and clinical confounders. Potential confounders include WHO stage of HIV disease, CD4+ count, plasma HIV-1 viral load, opportunistic infections, previous STIs and current use of anti-retroviral therapy.

**Specific Aim 4:** The goal of specific aim 4 is to determine the magnitude and duration of increased HIV-1 genital shedding that occurs after treatment with LEEP. Observed time trends in log copies of genital HIV-1 RNA will initially be evaluated via exploratory analyses of longitudinal measures based on scatter plot smoothing methods. Results will allow us to assess possible nonlinearities in trends, as well as investigate differences in results between subgroups of interest. The subgroups we are looking at include participants on HAART and who have CD4+ counts below 200. Further analyses will focus on estimation of post-LEEP changes from baseline levels in log copies of HIV-1 RNA using linear mixed effects regression methods. The primary predictor will be time on study (measured in weeks post-treatment). Initial models will include separate coefficients for each week of observation post-treatment (2, 4, 6, 10 and 14). Hypothesis 2 will be addressed directly via tests constructed about these coefficients. We will also explore the effect on results of adjustment for selected covariates, including demographic characteristics and baseline descriptors of participant health status.

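### Aim 4 addresses return to baseline after LEEP through significance tests on weekly coefficients and never defines return; such tests can support a rise but not a return

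*Protocol*

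**What the plan says.** Under Objectives, Hypothesis 4 has two parts: "There will be a significant increase in HIV-1 genital shedding post-treatment which will return to baseline before 14 weeks post-treatment". The matching null hypothesis is equal quantity before treatment, after it, and up to 14 weeks.

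Statistical Analysis, Specific Aim 4, gives the goal as the magnitude and duration of increased shedding. It plans smoothing of time trends, then estimation of changes from baseline in a linear mixed model with separate coefficients for weeks 2, 4, 6, 10 and 14. The hypothesis "will be addressed directly via tests constructed about these coefficients". The text there calls it Hypothesis 2, but in context it can only be the post-LEEP hypothesis. Study Design adds the proportion with detectable HIV-1 at each time point and the log difference from baseline, by individual and as a mean.

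The sample-size section for Aim 4 states "A sample size of 30 will provide sufficient power to address hypotheses of interest". It claims at least 80% power for a change "as small as 1 log as significant at the 5% level" and more than 95% for 1.5 logs. The calculation concerns baseline to week 1.

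No section gives a margin, a confidence-limit rule or any other definition of return to baseline.

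**The concern.** The duration of shedding is one of the two things Aim 4 sets out to measure, and it depends on deciding when shedding has ended. The inferential tool named for the hypothesis tests no change. Rejection supports the first half of Hypothesis 4. Failure to reject does not establish the second half: it may mean a return, or only that 30 women cannot resolve the remaining rise.

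If non-significance were taken as return, the error would have a direction. Noisier data or more missed visits would make shedding appear to end sooner. The Justification expects the results to bear on recommendations for post-procedure abstinence where a partner is HIV-negative or of unknown status, and Expected Application of Results says they will guide counselling. An apparent duration that is too short is the wrong direction for that use.

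**Working it through.** **Inputs** (Sample Size, Specific Aim 4): "We assume a standard deviation of 1.7 log copies for both the baseline and follow-up measure"; "the correlation between the baseline and follow-up measure will be 0.7"; "change will be evaluated using a t-test for paired measurements"; n = 30. Two-sided testing and complete follow-up are my assumptions, because neither is stated.

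**1. The plan's own figure.**
- SD of change = 1.7 × √(2 × (1 − 0.7)) = 1.317 log.
- SE = 1.317/√30 = 0.240 log.
- t(0.975, 29 df) = 2.045, so the 95% half-width is 2.045 × 0.240 = 0.49 log (3.1-fold).
- Noncentral t power for 1 log (noncentrality 1/0.240 = 4.16) is 98.0%, and for 1.5 log it exceeds 99.9%.

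Both stated lower bounds are therefore true. They concern changes of 1 log or more at week 1, not the smaller residual rises at late visits on which a claim of return depends.

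**2. Chance that a persisting rise is non-significant at one visit.**
- 0.3 log (2-fold): noncentrality 0.3/0.240 = 1.25, giving 77%.
- 0.5 log (about 3-fold): noncentrality 0.5/0.240 = 2.08, giving 48%.

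A simulated balanced random-intercept model with seven visits gave power of 24% for an exact 2-fold and 50% for an exact 3-fold rise, against 23% and 48% from the paired t-test. The paired test is a fair stand-in for the planned model.

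**3. Sensitivity to the variance.** The same section quotes a between-individual SD of 1.66 and a within-individual SD of 0.55. These imply a correlation of 1.66²/(1.66² + 0.55²) = 2.756/3.058 = 0.90. With r = 0.9, the SD of change is 1.7 × √0.2 = 0.760 and the SE is 0.139. The two probabilities become 45% and 6%.

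**4. Missing visits.** If 20 women attended week 14 (assumed), the SE would be 1.317/√20 = 0.294. At r = 0.7 the probabilities would rise to 84% and 64%.

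**5. A confidence-limit rule instead.** Call shedding returned at a visit when estimated change + t × SE is below margin m. The probability comes from the noncentral t with noncentrality (true rise − m)/SE. Per visit, n = 30:

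| True rise (log) | r | Non-significant | Upper limit < 1 log | Upper limit < 0.5 log |
|---|---|---|---|---|
| 0 | 0.7 | 95% | 98% | 52% |
| 0.3 | 0.7 | 77% | 80% | 12% |
| 0.5 | 0.7 | 48% | 52% | 2.5% |
| 0 | 0.9 | 95% | >99.9% | 94% |
| 0.3 | 0.9 | 45% | 99.8% | 29% |
| 0.5 | 0.9 | 6% | 94% | 2.5% |

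A 1 log margin is no better than non-significance at r = 0.7 and much worse at r = 0.9. A 0.5 log margin controls the error at 0.5 log whatever the correlation. Requiring the limit to stay below the margin at later visits lowers the figures for earlier visits but not for week 14.

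**The case against.** A reader might infer that the Protocol decides return by non-significance. It does not say so. It names coefficient tests and leaves return undefined. It also plans to estimate the change from baseline and to give detection proportions at every visit, so a persisting rise could remain visible in the results. This stands, and it limits the point to a missing definition and a tool that cannot fill it. It does not remove the point: neither the estimates nor the proportions come with a rule for return. Nor is this merely detail left to an analysis plan, because the Protocol itself says how the hypothesis will be addressed.

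A reader might also extend the criticism to Aim 3a, where Hypothesis 3 expects an "increase in genital HIV-1 RNA shedding that will return to baseline within 7 days post-procedure". The coefficient tests are written for Aim 4 only, and Aim 3a is described as an exploratory pilot without a sample-size calculation. The extension is not supported.

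A third tempting reading is that a 3-fold rise would often be missed. That holds at the adopted correlation of 0.7 (48%) but not at about 0.9 (6%). The 2-fold result is substantial under both.

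Finally, Aim 4 is said to provide preliminary data for a larger trial, which lowers the stakes. The same section nevertheless expects the findings to guide counselling.

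**Conclusion.** The point holds in this form: the second half of Hypothesis 4 has no definition and no method that could support it, so a return could be read only from failure to reach significance. On the adopted inputs, that reading would miss a persisting 2-fold rise at a given visit 77% of the time and a 3-fold rise 48%; at r of about 0.9, 45% and 6%. These are per-visit figures for 30 women with complete data and two-sided 5% tests. The stated power is correct for what it covers. This should be changed, because the correction is cheap and duration is a named goal.

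**What to change.** In Statistical Analysis, Specific Aim 4:

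- State that return to baseline will not be inferred from a non-significant coefficient.
- Report the mean change from baseline with its 95% CI at every post-LEEP visit.
- Call shedding returned only from the first visit at which the upper 95% limit is, and stays, below a margin that the investigators fix in advance. Otherwise report it as not shown to have returned.
- Do not use 1 log as the margin. In the sample-size section it is an effect to be detected, and nothing there says that smaller rises are negligible. It would label a persisting 0.5 log rise returned 52% (r = 0.7) to 94% (r = 0.9) of the time.
- Correct the hypothesis number in that paragraph.

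As an illustration only, a 0.5 log margin limits a false finding of return at a true 0.5 log rise to 2.5%. Rises below the margin get less protection, so its choice matters.

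For Aim 3a, report the day 2 and day 7 changes with their CIs and draw no formal conclusion about return.

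Cost: a few sentences, with no extra women or visits. The downside is inconclusive visits. With no true change and a 0.5 log margin, return would be shown at a given visit about 52% of the time at r = 0.7, or 94% at r = 0.9. Reaching 80% at r = 0.7 would take about (1.317 × (1.960 + 0.842)/0.5)² ≈ 55 women. With 30, an inconclusive result should be accepted and reported as such.

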**TIME FRAME/DURATION**

|  | July-Sept 2010 | Oct-Dec  2010 | Jan-March  2011 | April-June  2011 | July-Sept  2011 | Oct-Dec  2011 | Jan-March  2012 | April-June 2012 |
| --- | --- | --- | --- | --- | --- | --- | --- | --- |
| Hire and train project coordinator | X |  |  |  |  |  |  |  |
| Develop SOPs, Study Manual, Database | X |  |  |  |  |  |  |  |
| Train clinic and lab staff in protocols | X | X |  |  |  |  |  |  |
| Participant Enrollment and Specimen Collection |  | X | X | X | X |  |  |  |
| Specimen Processing and Evaluation |  |  | X | X | X | X |  |  |
| Analyze data |  |  |  |  | X | X | X |  |
| Present data at regional, national, or international meetings |  |  |  |  |  |  | X | X |
| Write and submit manuscript |  |  |  |  |  |  | X | X |

**EXPECTED APPLICATION OF RESULTS**

Specific Aims 1 and 2 will define the test characteristics for VIA and VILI as well as the parameters for a p16^INK4a^ biochemical assay for use in this population, which would be its first trial among HIV-infected women. This will provide not only a direct comparison, but will help validate the use of either or both low-cost tests in the setting of an HIV-care clinic. An ELISA-based biochemical assay can be developed into a simple test that can could be run immediately without water or electricity requirements, similar to a urine pregnancy, blood glucose or HIV-test. Development of a point-of-care test for a biomarker with high sensitivity and specificity for CIN will exponentially increase access to cervical cancer screening in resource-limited settings.

Specific Aims 3 and 4 will provide preliminary data for a larger trial looking at HR-HPV and HR-HPV-related high-grade CIN as risk factors for HIV-transmission. Aim 4 will provide preliminary data about the levels and time-course of post-treatment HIV-1 genital shedding, providing a better understanding of potential risks of cervical dysplasia treatment among HIV-infected women. These findings will guide pre- and post-procedure counseling to ensure women’s safety and minimize risk of HIV transmission as well as aid in the design of a randomized trial that incorporates HIV genital shedding as a safety outcome to be compared by treatment arms.

**BUDGET**

|  |  |  |  |  |  |  |  |
| --- | --- | --- | --- | --- | --- | --- | --- |
| ***Personnel*** | |  |  | *%* | *Salary* | *Benefits* | *Amount* |
| 251 | |  |  |  |  |  |  |
|  | PI: [name] |  |  | 85% | In-Kind |  |  |
|  | Study Coordinator-KEMRI/FACES |  |  | 100% | $9,600 | $2,021 | $11,621 |
|  | Study Clinician-KEMRI/FACES |  |  | 100% | $6,700 | $1,586 | $8,286 |
|  | Data Analyst/Project Asst-UCSF |  |  | 40% | $50,000 | $5,800 | $25,800 |
|  | Data Entry Clerk-KEMRI/FACES |  |  | 60% | $4,250 | $762 | $3,312 |
| *Sub-total: Personnel* | |  |  |  |  |  | $49,019 |
| ***Non-Personnel Operating Expenses*** | |  |  |  |  |  |  |
|  | |  |  |  |  |  |  |
|  | Genital Viral Load Testing |  |  |  |  |  | $25,110 |
|  | Serum Viral Load Testing |  |  |  |  |  | $3,100 |
|  | STI Testing |  |  |  |  |  | $12,600 |
|  | Pathology |  |  |  |  |  | $4,000 |
|  | Participant Reimbursement |  |  |  |  |  | $3,645 |
|  | Lab and Clinical Supplies |  |  |  |  |  | $10,800 |
|  | Equipment Maintenance |  |  |  |  |  | $600 |
|  | Specimen Shipment |  |  |  |  |  | $2,500 |
|  | Printing |  |  |  |  |  | $800 |
|  | Translation of Consents |  |  |  |  |  | $600 |
|  | Clinician Training (hall rental, meal) | |  |  |  |  | $335 |
|  | Telephone fees: Local and International |  |  |  |  |  | $1,800 |
|  |  |  |  |  |  |  |  |
|  | ***Operating Expenses Subtotal*** | |  |  |  |  | ***$65,098*** |
| **DIRECT COSTS US$** | |  |  |  |  |  | **$114,909** |
| **DIRECT COSTS Kenyan Shillings** | |  |  |  |  |  | **8,618,175**  **Ksh** |

Budget Justification

**PERSONNEL**

**Principal Investigator, [name], MPH, (salary support provided by KL2 award)**

As Principal Investigator, [name] will be responsible for the overall scientific governance and programmatic leadership of the study. [name] will provide oversight of implementation of all study components, including fiscal and administrative management of the study. She will hire and train the study coordinator, lead the development of the study protocol and manual of procedures, oversee submissions to ethical review committees for KEMRI and UCSF, train the study clinicians, and oversee enrollment of study participants and maintenance of good clinical practices. [name] will also visit the program site in Kenya at least twice to monitor program progress and to guide program development She will be in regular communication with the scientific collaborators and study coordinator through conference calls, meetings, and email correspondence.

**Study Coordinator (FACES), TBD (12 calendar months)**

An on-site study coordinator will be essential for the smooth functioning of the research project. Responsibilities include assisting the PI with implementation of the protocol, coordinating communication with the KEMRI ethical review committee, ensuring that the recruitment and follow-up goals of the study are met, providing guidance in study-related procedures and good clinical practice to study clinicians, and providing general day-to-day study administration. He/she will be in regular communication with the PI via phone and email. He/she will have training s a nurse and significant experience in research.

**Study Clinician (FACES), TBD (12 calendar months)**

The study clinician will assist the study coordinator in carrying our the clinical tasks as part of the study visits, including the study-related colposcopy and specimen collection. This person will under good clinical practices and study-specific training and will assist the study coordinator and PI in day-to-day management and continued implementation of the study.

**Data Analyst/Project Assistant (UCSF), TBD (4.8 calendar months)**

The Data Analyst/Project Assistant will assist the PI in submission of ethical review committee documents throughout the duration of study, development of training materials and the study manual of operations, creation of the participant database and SOPs for the Kenyan-based data clerk and preparation of study forms and documents. In collaboration with Dr. [name], he/she will be responsible for cleaning, managing, and analyzing data collected from study sites for analysis and reporting. Fringe benefits for UCSF personnel are calculated at 29%.

**Data Entry Clerk (FACES), TBD (6.6 calendar months)**

The data entry clerk will with the Data Analyst/Project Assistant to create the study database and will be responsible for verifying that data is entered with accuracy, completeness and consistency. He/she will also maintain orderliness and confidentiality of participants’ paper files.

KEMRI contract personnel are paid a 15% gratuity at the end of their contract period and benefits include medical insurance cover at $490 per person, based on percent effort, Worker’s Injury Benefit Insurance at $59 per person and the NSSF contribution of $2.65 per calendar month of employment.

**OTHER**

**Laboratory Testing:**

**Cervico-vaginal HIV-1 Viral Loads ($25,110)**

Viral load testing will be performed with the assistance of [name] through the ARI-UCSF LCV/CFAR Virology Core Lab. There will be a total of 100 participants: 50 women with no evidence of cervical dysplasia who have a single cervico-vaginal viral load and 50 women with cervical dysplasia who have one baseline visit (100). Thirty women will be part of the longitudinal study and seven follow-up visits (210). The tests are $81 each, including the strips and collection containers. Storage will be provided in the freezers of the research laboratory in the FACES clinic. Total: 310*81=$25,110.

**Serum Viral Load Testing ($3,100)**

Viral load testing is available through a clinical and research facility affiliated with the University of Nairobi and University of Washington in Nairobi at $31.00 per test. All 100 women in specific aims 1 and 2 will have baseline serum viral load testing. Total: 100*31=$3,100.

**STI Testing ($12,600)**

NAAT Testing for sexually transmitted infections will be carried out in a local facility at approximately $7 per test. Total: 1800*6=$12,600.

**Pathology Reading ($4,000)**

Pathology specimens will be read by a trained pathologist at KEMRI, with whom there is an established relationship for FACES and the cervical cancer screening program. From our current rate of positive colposcopies and detection of CIN2/3, we have estimated that approximately 500 specimens will be read at $8 per specimen for this study. The UCSF pathologist has agreed to provide a second read of the prepared specimens at no extra fee. Total: 500*8=$4,000.

